### Statistical and health economic analysis

Analyses of recurrence will be performed using generalised estimating equations (GEE) using the binomial family and the logit link treatment arm and grade of haemorrhoid as fixed effects, with surgeon being incorporated as a clustering term. The difference in proportions and its associated CI will be derived using the delta method [15]. Pain scores at day seven will be analysed using GEE with an identity link; the fixed effect covariates will be treatment arm, grade of haemorrhoid and pre-procedure pain rating, with surgeon again incorporated as a clustering term. Secondary endpoints will be analysed analogously. Unadjusted analysis (difference between arm and 95% CIs) will be reported alongside adjusted analysis.

Safety will be assessed by (i) post-surgical complications and (ii) postsurgical complications leading to SAE, both of which will be summarised for each arm by the number of participants experiencing (a) each complication type at least once and (b) any complication at least once.

The primary analysis will use the Intention to Treat (mITT) population (we do not follow-up participants who withdraw before surgery). For the primary outcomes only, Per Protocol (PP) and As Treated (AT) populations will be considered for sensitivity analysis. There is no a priori defined sensitivity analysis for secondary outcomes.

We will use an interaction statistical test between intervention arm and subgroups to directly examine the strength of evidence for the between arm difference varying between subgroups for the primary outcomes. Age and grade of haemorrhoid will be the only a priori defined sub-groups to be considered for interaction test. Sub-group analysis will be performed regardless of the statistical significance on the overall intervention effect.

Case and item missing data will be examined and multiple imputation methods will be used to reduce bias due to any missing responses in the analyses. Where appropriate, modelling methods that generate robust standard errors (SEs) in the presence of missing data will be considered.

We will separately calculate the primary outcomes for each of the three surgical options in the control arm and will calculate for each of them the difference (and associated 95% CI) between (1) RFA and haemorrhoidopexy; (2) RFA and, HAL; and (3) RFA and haemorrhoidectomy. It should be noted that these are exploratory (and non-randomised) comparisons and not subject to the benefits of randomisation; as the characteristics of the control surgery sub-groups may not be balanced when compared to RFA.

For the cost-effectiveness analysis, the area under the curve method will be used to analyse EQ5D and estimate Quality Adjusted Life Years (QALYs) for each individual.

Resource use is collected for the following categories: the direct costs of surgery, the costs of treating recurrence, other complications, and any other relevant NHS resource use. An NHS perspective will be used for costing resource use.

Unit costs, to apply to each category of resource use will come from sources widely used in economic evaluations such as NHS Reference Costs, NHS supply systems, British National Formulary and ‘Unit Costs of Health and Social Care’ published by the PSSRU. Where necessary, we will supplement these unit costs with local sources such as the finance departments of participating hospital trusts.

The analysis will use multiple imputation methods for missing data. For each individual we will estimate total costs and QALYs over the 12-month follow-up period. The mean costs and QALYs for each comparator will be estimated and regression analysis used to adjust for baseline characteristics of patients assigned to each arm. Bootstrap methods will be used to generate the cost-effectiveness plane and associated cost-effectiveness acceptability curve.

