### Sample size

The target sample size is 376 participants (188 per arm) and is based on two co-primary endpoints: (i) a non-inferiority design for recurrence and (ii) superiority design for pain at 7 days. Previous research has demonstrated RFA is associated with a recurrence rate of 4% to 15%, compared with 15% for haemorrhoidectomy and 25–30% for HAL. Our patient panel members have advised us that RFA would be acceptable if we could rule out a 10% increase in recurrence, which we have used as our non-inferiority limit, accompanied by a reduction in pain. The trial will recruit 376 participants (188 per arm), which provides 90% power to declare non-inferiority based on a 15% drop out, an Intraclass Correlation Coefficient (ICC) of 1% among 16 surgeons, a one-year recurrence rate of 15% for intervention and 20% for usual care, a non-inferiority limit of 10% and a one-sided 2.5% significance level. These assumptions are heavily based on our previous HubBLe trial which found a 12% drop-out in the HAL surgery arm and a zero ICC for 12-month recurrence [6]. A sample size of 376 ensures a 90% power to detect a minimal clinical importance difference (MCID) of 0.6 points (1/3rd of a standard deviation) in Numeric Pain Rating Scale-reported pain at 7 days at the two-sided 5% level assuming 5% missing data, a correlation of 0.5 between baseline and follow up and an ICC of 1%. No adjustment for multiple testing is necessary since RFA will need to demonstrate significance on both endpoints.

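### Both co-primary tests rest on a surgeon-clustered GEE with a planned 16 clusters; with the usual uncorrected robust standard errors they would run above their stated error levels, so a small-sample correction should be pre-specified

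*Protocol article*

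**What the plan says.** In the protocol article, under Statistical and health economic analysis, recurrence is modelled by GEE (binomial family, logit link) with "treatment arm and grade of haemorrhoid as fixed effects, with surgeon being incorporated as a clustering term". The effect is then put on the risk-difference scale: "The difference in proportions and its associated CI will be derived using the delta method". For pain, "Pain scores at day seven will be analysed using GEE with an identity link", and "the fixed effect covariates will be treatment arm, grade of haemorrhoid and pre-procedure pain rating, with surgeon again incorporated as a clustering term".

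The number of clusters comes from the Sample size section, which assumes "an Intraclass Correlation Coefficient (ICC) of 1% among 16 surgeons". The same section sets the error levels: one-sided 2.5% for recurrence against a 10-point margin, and two-sided 5% for pain. RFA must succeed on both endpoints, and for that reason no multiplicity adjustment is made.

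For the primary GEE the article states no variance estimator, working correlation, small-sample correction or reference distribution. Its one mention of robust standard errors concerns missing data.

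**The concern.** The customary inference after a GEE uses the sandwich variance and treats the Wald statistic as normal. Both steps are justified when there are many clusters. With 16, the uncorrected sandwich variance is too small on average and is itself imprecisely estimated, so confidence limits are too narrow and tests reject too often.

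Here this affects both claims on which the trial turns. On recurrence, an interval that is too narrow makes it easier to declare RFA non-inferior when it is in truth 10 points worse. Requiring success on both endpoints does not help, because that rule protects the overall error only if each test holds its own level. If RFA truly reduces pain but sits at the recurrence margin, the chance of a false overall claim approaches the error rate of the recurrence test alone.

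**Working it through.** **Inputs from the Sample size section.** 376 participants (188 per arm); 16 surgeons; ICC 1%; recurrence 15% (RFA) v 20% (control); margin 10 points; one-sided 2.5%; 15% drop-out. For pain: difference 0.6, one third of an SD, so SD 1.8; two-sided 5%; 5% missing; correlation 0.5. Power is 90% for both.

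**Step 1: reproduce the plan's sample size.**
- Recurrence: (0.15×0.85 + 0.20×0.80) × (1.960 + 1.282)² / (0.10 + 0.05)² = 0.2875 × 10.507 / 0.0225 = 134.3 per arm. Evaluable participants per surgeon: 376 × 0.85 / 16 = 19.98. Design effect: 1 + 18.98 × 0.01 = 1.190. Required: 134.3 × 1.190 / 0.85 = 187.9 per arm, which matches 188.
- Pain: 2 × (1.8 × 3.2415 / 0.6)² = 189.1; × (1 − 0.5²) = 141.9; design effect 1 + (376 × 0.95 / 16 − 1) × 0.01 = 1.213; 141.9 × 1.213 / 0.95 = 181.2 per arm. Power at 188 is 91.0%, consistent with the stated 90%.

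The match for recurrence shows that 16 clusters is the figure the plan actually used.

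**Step 2: rough analytic check.** Suppose the robust standard error were unbiased but had only 15 degrees of freedom. Referring the statistic to ±1.96 would then give P(t15 > 1.96) = 3.4% one-sided and 6.9% two-sided. In simulation the uncorrected standard error averaged only about 0.94-0.95 of the true value with equal surgeon volumes (0.93-0.94 with unequal volumes), which adds to this.

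**Step 3: simulated error rates.** There were 5,000 trials per setting, with individual 1:1 randomisation within surgeon. Recurrence: 320 analysed, true rates 30% v 20% (the margin), logit GEE, delta-method risk difference. Pain: 357 analysed, no true effect, identity link, baseline covariate. Monte Carlo standard error is about 0.3 points (recurrence) and 0.4 points (pain). Each cell gives recurrence / pain, to be compared with 2.5% / 5%.

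| 16 surgeons | Uncorrected robust, normal | Mancl-DeRouen, t15 | Model-based, normal |
|---|---|---|---|
| Equal volumes, ICC 0 | 3.5% / 7.8% | 1.9% / 4.5% | 2.3% / 5.1% |
| Equal volumes, ICC 1% | 3.7% / 7.7% | 2.1% / 4.4% | 2.4% / 5.1% |
| As above, plus surgeon-by-treatment variance of 1% of total | 3.7% / 8.1% | 2.0% / 4.6% | 3.0% / 6.3% |
| Unequal volumes (CV 0.65), ICC 1% | 4.2% / 9.2% | 2.4% / 5.2% | 2.7% / 5.3% |

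Rows use an exchangeable working correlation; an independence structure, where it was run, gave almost the same figures. Separate simulations with other random draws and other assumed volumes put the uncorrected errors at up to 4.5% for recurrence and between 7.6% and 9.0% for pain. With 32 surgeons the uncorrected errors were 3.1% and 6.8%.

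**Step 4: does a varying comparator matter?** The article cites recurrence of 15% after haemorrhoidectomy and 25-30% after HAL. Suppose half the surgeons have control recurrence of 15% and half 27.5%. Recurrence error was then 2.8% (equal volumes) and 3.6% (unequal) with model-based standard errors, 3.5% and 4.3% with uncorrected robust ones, and 1.7-2.3% with the correction.

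**The case against.** A reader might infer that both co-primary tests, as planned, exceed their stated error rates. The document does not support that. It never says that uncorrected robust standard errors will be used. The variance estimator and its degrees of freedom are commonly settled in the statistical analysis plan, which is not shown and may name a correction. The same GEE on the same 16 clusters can hold its level: the corrected version does, and so do model-based standard errors when the effect is common to all surgeons. All of this stands, and it makes the point conditional.

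Sixteen is also a planning figure. It equals the number of hospitals, and nothing limits a hospital to one surgeon. This stands in part: more surgeons would reduce the inflation, but at 32 it had not gone. The upper figures depend on unequal surgeon volumes, which the documents do not give. Nor do the simulations include the planned multiple imputation.

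Two defences do not stand. The zero ICC for recurrence in the sponsor's previous trial gives no protection, because the inflation comes from estimating a variance from few clusters and is present at ICC 0. And model-based standard errors are not a safe default: the control procedure is the surgeon's choice among three operations, and the article's own figures give them different recurrence rates.

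**Conclusion.** The concern holds in conditional form. The article fixes the method, the clustering unit, the interval method and the planned number of clusters. Run in its customary form, that combination misses the stated levels: about 3.5-4.5% instead of 2.5% for non-inferiority (1.4 to 1.8 times) and about 7.5-9% instead of 5% for pain (1.5 to 1.8 times).

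These sizes assume about 16 surgeons who each treat patients in both arms, an even split of haemorrhoid grade with assumed grade effects, and equal or moderately unequal surgeon volumes. The direction does not depend on the ICC. Because the variance estimator is not stated and the analysis plan is not shown, this is a specification that should be made before the data are seen. It is not a demonstrated error, and it should not be classed as a must-fix.

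**What to change.** Keep the GEE. State that both co-primary analyses will use a bias-corrected sandwich variance (for example Mancl-DeRouen), with a t reference on the number of surgeons minus 1 degrees of freedom, and that the corrected variance enters the delta-method interval for the risk difference. If the statistical analysis plan already says this, no change is needed beyond confirming it. It should be fixed in advance, because a standard error chosen after seeing the data would be open to challenge.

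The cost is a sentence of analysis wording, a software option and slightly wider intervals. Simulated non-inferiority power at 15% v 20% falls from about 95% to about 88-90%, still close to the 90% planned. There is room for this because the sample size was multiplied by 1.19 for clustering. With 188 × 0.85 = 159.8 evaluable per arm and no design effect, the standard error is √(0.2875 / 159.8) = 0.0424, and 0.15 / 0.0424 − 1.96 = 1.58, which corresponds to about 94% power. When both arms are treated within each surgeon, that allowance is largely unused and absorbs most of the loss.

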### Participant recruitment and timeline

Patients will be recruited from 16 UK NHS hospitals over a 14-month recruitment period. The patients care team will conduct an initial case note review for eligibility. Potential participants will receive an approved Participant Information Sheet and given the opportunity to ask questions from both the surgical and research team at their hospital before enrollment into the trial. Participants will be approached either by the local Principal Investigator (PI) or a delegated team member with the appropriate Good Clinical Practice (GCP) training. Participants will give written consent either by remote postal consent, or face to face at surgical outpatient’s clinics. Reasons for non-consent will be recorded where possible and monitored by the study team.

After consent participants will be individually randomised in equal proportions at all centres using a remote, web-based randomisation system.*Group A*: RFA using the Rafaelo^®^ device or*Group B*: Surgeons’ choice of other procedures currently available in the UK NHS.

Baseline data will be collected on the day of surgery or up to 4 weeks before surgery. Details of the procedure will be recorded during or shortly after the surgery. Following the procedure data will be collected to establish scores of pain, as well as which patients have further treatment for recurrent symptoms or complications. This will be achieved using follow-up telephone questionnaires at 1, 7 and 21 days; at a clinic visit around 6 weeks after the intervention; and by interrogating hospital records, asking the patients consultant and writing to the patients GP at the 12-month follow-up. A summary of the participant involvement can be found in Fig. 1.

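### Non-inferiority on recurrence is decided on the as-randomised set alone, so crossover to a control operation could hide part of a true excess; the per-protocol result should have to agree.

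*Protocol article*

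**What the plan says.** Under Sample size, the protocol article bases the trial on "i) a non-inferiority design for recurrence and (ii) superiority design for pain at 7 days". The margin comes from patient advice that RFA would be acceptable "if we could rule out a 10% increase in recurrence, which we have used as our non-inferiority limit". RFA must succeed on both endpoints.

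Under Statistical and health economic analysis, one population serves both endpoints: "The primary analysis will use the Intention to Treat (mITT) population (we do not follow-up participants who withdraw before surgery"). The other sets have a supporting role: "For the primary outcomes only, Per Protocol (PP) and As Treated (AT) populations will be considered for sensitivity analysis". Nothing requires the per-protocol result to agree before non-inferiority is declared.

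The article does not say in words that participants who receive the other arm's operation are counted as randomised. That follows from the intention-to-treat name and from as-treated being listed as a separate set.

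**The concern.** For a superiority test, mixing of treatments between arms shrinks the difference and makes success harder. For a non-inferiority test on a harm such as recurrence, when RFA really is worse, the same shrinkage makes success easier.

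Some crossover is foreseeable. Listing an as-treated set presupposes it. Allocation comes before the operation ("After consent participants will be individually randomised in equal proportions at all centres"), with surgery later. RFA needs a specific device, while the three control operations are already available in the NHS.

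At stake is a claim that RFA is no worse on recurrence by more than 10 points. The Introduction says the result will inform whether RFA enters the treatment algorithm or health services disinvest. The pain endpoint is not a full safeguard: if RFA truly hurts less, pain will usually succeed whatever happens to recurrence.

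**Working it through.** **Inputs from Sample size.**
- Rates, margin and level: "a one-year recurrence rate of 15% for intervention and 20% for usual care, a non-inferiority limit of 10% and a one-sided 2.5% significance level".
- Size, power and loss to follow-up: "The trial will recruit 376 participants (188 per arm), which provides 90% power to declare non-inferiority based on a 15% drop out".
- Clustering: intraclass correlation 0.01, with 16 surgeons.

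**Reproducing the plan's figure.**
- Before inflation: n per arm = (0.15×0.85 + 0.20×0.80) × (1.96 + 1.2816)² / (0.10 + 0.05)² = 0.2875 × 10.507 / 0.0225 = 134.3.
- Analysed participants per surgeon: 376 × 0.85 / 16 = 19.975. Design effect: 1 + 18.975 × 0.01 = 1.190.
- Recruited: 134.3 × 1.190 / 0.85 = 188 per arm, total 376.

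The stated sample size reproduces at 90% power and is not in dispute. The effective number per arm is 188 × 0.85 / 1.190 = 134.3, used below.

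**Error at the margin, as randomised.** Let true recurrence be 30% on RFA and 20% on control, and let a fraction c of the RFA arm receive a control operation and have control-like recurrence. Then p_R = 0.30(1 − c) + 0.20c, SE = √[p_R(1 − p_R)/134.3 + 0.20×0.80/134.3], and error = Φ[(0.10 − (p_R − 0.20))/SE − 1.96]. The values of c are assumptions.

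| Crossover | Difference as randomised | SE | One-sided error (formula) |
|---|---|---|---|
| none | 10.0 points | 0.0525 | 2.5% |
| 5% RFA to control | 9.5 | 0.0523 | 3.1% |
| 10% RFA to control | 9.0 | 0.0522 | 3.8% |
| 15% RFA to control | 8.5 | 0.0520 | 4.7% |
| 5% both ways | 9.0 | 0.0526 | 3.8% |
| 10% both ways | 8.0 | 0.0526 | 5.7% |

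Simulation with whole-number counts runs 0.1 to 0.2 points higher throughout: 2.6% with no crossover, 3.2% at 5%, 4.0% at 10%, and 5.9% at 10% both ways. Allowing for both methods, the rounded values are 3.1%, 3.9% and 4.8% for 5%, 10% and 15%, and 5.9% for 10% both ways. Ignoring clustering (160 per arm) gives 3.2%, 4.0% and 5.0%.

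**Error when both sets must succeed.** If crossover is unrelated to prognosis, PP alone stays at 2.5% by formula (2.6% to 2.7% simulated). Requiring both mITT and PP gives about 2.4% to 2.5%.

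**Power under the planned 15% v 20% (simulated, 376 participants).**

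| Crossover each way | mITT alone | mITT and PP | Extra cost |
|---|---|---|---|
| none | 90% | 90% | 0 |
| 5% | 87.8% | 86.4% | 1.4 points |
| 10% | 85.3% | 83.1% | 2.2 points |

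**Pre-surgery withdrawals.** If a fraction w per arm is never operated on and has the same outcome in both arms, keeping them shrinks the 10-point difference to 10(1 − w): 9.5 points at 5% and 9.0 at 10%. The error is then 3.1% or 3.8%, taking 50% recurrence in the unoperated as an assumption. Excluding them equally leaves it at 2.5%.

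**The case against.** The strongest defence is that an as-randomised primary set with PP in support is an accepted convention for a pragmatic trial. PP and as-treated analyses are already named for both primary outcomes, and the reading of discordant sets is often left to the analysis plan. PP exclusions can themselves be prognostic. The size of the problem depends on crossover rates that the article does not give, and on RFA being exactly at the margin when the design expects it to be 5 points better. In that planned case, crossover counts against RFA by lowering power. The overall claim also needs pain superiority, which crossover weakens too.

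Much of this stands as a limit on size. It does not remove the point. The article states which set decides and gives PP only a sensitivity role, so this is a stated choice and not an omitted detail. Error control is judged at the margin. The possible bias in PP is a reason to require both sets and not to rely on PP alone.

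A reader might also infer that leaving out participants who withdraw before surgery makes a false non-inferiority claim easier. The article does not support that. With similar withdrawal in both arms, exclusion is neutral, or mildly protective compared with keeping untreated people. It would bias the result only if withdrawal depended on both arm and prognosis, in either direction, and participants are blinded. An all-randomised recurrence analysis is not the remedy: recurrence is timed from the procedure, so it is undefined for people who had none, and including them would dilute the difference. The abbreviation mITT after the words intention to treat is an editorial slip, because the same sentence discloses the modification.

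**Conclusion.** The point holds for crossover only. Letting mITT alone decide recurrence raises the one-sided risk of a false non-inferiority claim from 2.5% to about 3.1%, 3.9% or 4.8% at 5%, 10% or 15% RFA-to-control crossover, and to about 5.9% at 10% both ways. These figures assume true recurrence of 30% v 20%, about 134 effective participants per arm, and crossovers who have the recurrence risk of the operation they received. The inflation is moderate and conditional on crossover occurring. It is worth correcting because the PP analysis is already planned.

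**What to change.** For recurrence only, state that non-inferiority will be declared if the upper limit of the confidence interval for the difference (RFA minus control) is below 10 points in both the mITT and the PP set. Keep mITT as the primary set for pain. Say explicitly that crossovers are analysed as randomised in mITT, and write the set's name out as modified intention to treat. Report the number of pre-surgery withdrawals and their reasons by arm; no further analysis of them is needed.

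No new data are required. At 376 participants, power for recurrence would be about 86% with 5% crossover each way and 83% with 10%. Most of the fall from 90% is due to crossover itself; the added requirement accounts for 1 to 2 points, and the article should acknowledge it. If 90% power were wanted on PP alone, the total would be about 396 with 5% excluded per arm (188/0.95 = 198 per arm) or 418 with 10% excluded (188/0.90 = 209 per arm).

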### Intervention

The intervention is RFA (using the Rafaelo^®^ device, Modern Aesthetic Solutions Ltd, UK). The control arm is surgeon choice of surgery, which could be one of stapled haemorrhoidopexy, HAL or haemorrhoidectomy (consistent with international guidelines [3]). ORION will be a pragmatic trial; all procedures will be conducted as per standard care at individual hospitals. RFA has NICE approval where there are arrangements for clinical governance, consent, and audit or research [7].

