### Patients randomised to surgeon’s choice of other procedures currently available in the UK

The alternative therapies vary, and often depends on the preference of the surgeon. Stapled haemorrhoidopexy, HAL and haemorrhoidectomy are all available in the UK NHS and appropriate conventional therapies according to international guidelines [3]. The control arm will therefore comprise the ‘surgeon’s choice’ of operation based on one of these three options.

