### Assignment of intervention

A web-based randomisation system will generate random assignment with stratification by hospital. Research staff at hospitals will enrol participants on the randomisation system. Outcome assessors, statistician and participants will be blinded to allocation. In the event a patient or clinician needs to reveal allocation this is accessible through the unblinding procedure on the randomisation system.

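### The RFA contrasts with each control operation are confounded by the choice of operation; recording the intended operation before allocation would allow randomised, though still exploratory and less precise, versions

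*Protocol article*

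**What the plan says.** The Intervention section defines the comparator: "The control arm is surgeon choice of surgery, which could be one of stapled haemorrhoidopexy, HAL or haemorrhoidectomy". On how the operation is chosen, the section on the control arm says "The alternative therapies vary, and often depends on the preference of the surgeon", and the Introduction adds that treatment follows the severity of symptoms and the degree of prolapse.

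Under Statistical and health economic analysis, each primary outcome is to be calculated separately for the three control operations. A difference and 95% CI is then given for RFA against haemorrhoidopexy, HAL and haemorrhoidectomy in turn. The article notes that "these are exploratory (and non-randomised) comparisons and not subject to the benefits of randomisation", because "the characteristics of the control surgery sub-groups may not be balanced when compared to RFA".

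Two other statements fix what is known before allocation. Under Assignment of intervention: "A web-based randomisation system will generate random assignment with stratification by hospital". Under Participant recruitment and timeline: "Details of the procedure will be recorded during or shortly after the surgery". Nowhere does the article ask, before randomisation, which operation a participant would receive if allocated to control.

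**The concern.** Each contrast uses all RFA participants on one side and a selected part of the control arm on the other. Selection has two routes. Patients with different prolapse or symptoms may be steered to different operations. Surgeons and hospitals that favour one operation will also be over-represented in that control subset, while the RFA arm spans all of them, so the hospital balance that stratification provides is lost.

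These contrasts are how a reader would learn which operation RFA might replace. The Sample size section cites recurrence of 4% to 15% for RFA, "compared with 15% for haemorrhoidectomy and 25–30% for HAL", so the pooled control rate averages over procedures that are expected to differ. The article accepts the confounding as a limitation, although a small change at randomisation would avoid it.

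**Working it through.** **The plan's own figure.** Inputs from the Sample size section: recurrence 15% v 20%, margin 10 points, one-sided 2.5%, 90% power, ICC 1%, 16 surgeons, 15% drop-out.
- Distance to the margin: 0.10 + (0.20 − 0.15) = 0.15. Variance sum: 0.15×0.85 + 0.20×0.80 = 0.1275 + 0.16 = 0.2875. This needs 135 per arm.
- Cluster size 376×0.85/16 ≈ 20.0; design effect 1 + (20.0 − 1)×0.01 ≈ 1.19.
- 135×1.19/0.85 ≈ 189 per arm, 378 in total against the stated 376; power at 376 is 90.0%. The sample size is not in dispute.

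**Bias of the planned contrasts.** Suppose RFA and every operation have the same effect, so that any expected difference is bias. Let stratum k (patients whose surgeon would choose operation k) have share s_k and risk r_k. The planned contrast then has bias Σ s_j r_j − r_k. The article gives neither shares nor risks by stratum, so all of these values are assumptions.

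| Shares | Risks | Overall risk | Bias by stratum (points) |
|---|---|---|---|
| 45/45/10% | 10/20/15% | 15.0% | +5.0, −5.0, 0.0 |
| 45/45/10% | 12/18/15% | 15.0% | +3.0, −3.0, 0.0 |
| 60/30/10% | 10/20/15% | 13.5% | +3.5, −6.5, −1.5 |
| 60/30/10% | 12/18/15% | 14.1% | +2.1, −3.9, −0.9 |
| equal thirds | 10/20/15% | 15.0% | +5.0, −5.0, 0.0 |
| equal thirds | 12/18/15% | 15.0% | +3.0, −3.0, 0.0 |
| any | equal | – | 0, 0, 0 |

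The first row was simulated (10,000 trials, 160 evaluable per arm). Coverage of the nominal 95% CI for the planned contrasts was 77%, 87% and 89%. Within strata declared before randomisation, bias was 0.0 to 0.1 points and coverage 94–95%. The 89% belongs to a stratum with no bias and about 16 controls, so it reflects small numbers and not confounding.

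**Cost in precision.** Evaluable n is 188×0.85 ≈ 160 per arm, with rates 15% and 20% and no design effect. For stratum share p:
- planned SE = √(0.1275/160 + 0.16/(160p))
- within-stratum SE = √(0.2875/(160p))
- ratio = √(0.2875/(0.1275p + 0.16))

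| p | Planned SE | Within-stratum SE | Increase |
|---|---|---|---|
| 1/2 | 0.053 | 0.060 | 13% |
| 1/3 | 0.062 | 0.073 | 19% |
| 1/10 | 0.104 | 0.134 | 29% |

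**When mean squared error improves.** The within-stratum estimate has the smaller mean squared error only if the bias removed exceeds √(0.1275/160 × (1/p − 1)). That is 2.8 points at p = 1/2, 4.0 at 1/3 and 8.5 at 1/10.

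**Power.** Within declared strata, non-inferiority power under the trial's own rates is about 20%, 53% and 78% for shares of 10%, 33% and 60%.

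**The case against.** The strongest reply is that nothing here is misstated. The trial asks a pragmatic question, RFA against surgeon's choice, and the article labels the operation-specific contrasts correctly and explains why. That stands: this is an avoidable weakness in a secondary analysis, not an error.

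Grade of haemorrhoid is already in the primary-outcome models. If the same models serve these contrasts, imbalance in grade is largely dealt with, so a bias argued from grade alone would not carry the point. Selection on other patient features and on surgeon or hospital remains. Treating surgeon as a clustering term corrects the standard error, not this imbalance.

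The precision cost is also real. In a small stratum the randomised estimate may be no closer to the truth on average; what it gains is freedom from selection bias and an interval that keeps its coverage.

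Finally, research staff enrol participants and consent can be postal, so the article does not show that the surgeon's choice is known at randomisation. The new field assumes that it can be obtained. The full protocol might already record intent, but calling the contrasts non-randomised argues against that.

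**Conclusion.** The planned contrasts are confounded by patient selection and by surgeon or hospital preference, and most of this can be avoided cheaply. The size of the bias is unknown from the document. Under the assumed shares and risks it is about 2 to 6.5 points in the lowest-risk and highest-risk strata, and it is zero if risk does not differ by intended operation.

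Stronger readings are not supported:
- A reader might infer that the trial's main result is affected. It is not: the comparison of RFA with surgeon's choice is randomised, and neither co-primary analysis nor the sample size changes.
- A reader might take the 10 to 15 point gap between 15% and 25–30% as the bias. It is a difference in prior recurrence between operations, and the article sets no non-inferiority test for these contrasts against the 10-point margin.
- A reader might expect the change to give fully randomised comparisons with each operation. It gives comparisons with the intended operation. If surgeons depart from the declaration, the operation performed will differ, and comparisons among the three control operations stay non-randomised.

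With the power shown above, the results remain exploratory.

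**What to change.** For participants not yet randomised, add one mandatory field to the web randomisation form: the operation intended if the participant is allocated to control. It should be agreed with the surgeon and locked before allocation is shown.

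Estimate RFA v control within each declared-operation stratum, with both arms analysed as randomised and grouped by declared rather than performed operation. Make this the main version of the operation-specific contrasts. Keep the present contrasts as a supplement labelled non-randomised; participants already randomised contribute only there. State that the results are exploratory and refer to the intended operation. Stratifying randomisation on the new field is optional, and adding it to the primary models is not needed.

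The cost is one form field, a step to obtain the surgeon's intention before randomisation, a change of analysis wording, and wider intervals. No extra participants are required. If recruitment is already under way, which the article does not say, the strata will be smaller and the intervals wider than calculated here.
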